### Statistical Analysis

Data will be analyzed using IBM SPSS version 21.0 software. Differences between sociodemographic characteristics for the intervention and control groups will be tested using chi-square and *t* tests. A mixed between-within subjects ANOVA will be employed to compare the mean difference of the psychoeducation intervention program between the two groups at pretest, posttest (week 5), and at 2-months of follow-up (week 12). The magnitude effect size of the intervention program will be calculated using Cohen’s formula. Analyses will be conducted based on the intention-to-treat principle and for all completers.

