### Recruitment

A total of 1556 participants participated in the first phase of this study, entitled “Contributing Factors of Common Mental Health Disorders in Selangor.” Out of these, 634 participants provided complete contact information. This serves as the sampling frame in this study. A team of trained enumerators will visit the participants’ households to brief them about the study. Their personal particulars will be updated and their Internet literacy will be checked.

Eligible participants will be invited to participate in the study (second phase) through a phone call by a trained research assistant. They will be briefed about the study again. A respondent information sheet containing detailed information about the study, website log-in information, and a consent form will be emailed to the participants. After consenting to participate in the study, the participants will complete the baseline online assessment and then will be randomly allocated to either the intervention or the control group (Figure 1).

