### Outcome Measures

#### Primary Outcome Measure

The primary outcome of this study will be the change in depressive and anxiety symptoms. This is defined by a change in the sum score on the Patient Health Questionnaire 9 (PHQ-9) and Generalized Anxiety Disorder 7 (GAD-7) between the baseline and follow-up assessments at weeks 5 and 12.

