#### Secondary Outcome Measure

The secondary outcome of this study will be the change in the mental health literacy score. This is defined by a change in the total score on the Mental Health Literacy Questionnaire (MHLQ) between the baseline and follow-up assessments at weeks 5 and 12 (Table 1).

**Table 1 table1:** Overview of measurements.

Instrument	Aim	Time of measurement		
		T_0_ (Baseline)	T_1_ (Posttest at week 5)	T_2_ (Follow-up at week 12)
Sociodemographics	Characteristics of participant	Yes		
PHQ-9	Symptoms of depression	Yes	Yes	Yes
GAD-7	Symptoms of anxiety	Yes	Yes	Yes
MHLQ	Mental health literacy	Yes	Yes	Yes

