### Sample Size

The sample size for this study was calculated using a formula by Lemeshow et al [29]: n=(2σ^2^[Z_1−α/2_+Z_1−β_]^2^)/([μ_1_−μ_2_]^2^).

Using a power of 80%, a confidence interval of 95%, a pooled standard deviation of 9.865, and a baseline and posttest mean score of 21.1 and 16.2, respectively, in the intervention group [11], the calculated sample size was estimated to be 64 participants. Taking into consideration a 30% dropout rate [30], the final sample size calculated was 84 participants in each group.

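### Pretest is analysed as a third outcome occasion instead of a covariate: a valid test of change, but one that gives up precision from baseline scores already collected

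*Protocol article*

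**What the plan says.** The Statistical Analysis section of the protocol article fixes the model: "A mixed between-within subjects ANOVA will be employed to compare the mean difference of the psychoeducation intervention program between the two groups at pretest", and the sentence goes on to list week 5 and week 12. The Results paragraph of the abstract likewise plans a series of mixed ANOVAs. Neither place mentions baseline as a covariate, and neither says which term of the model carries the efficacy conclusion.

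Under Primary Outcome Measure, "The primary outcome of this study will be the change in depressive and anxiety symptoms", defined as the change in PHQ-9 and GAD-7 sum scores "between the baseline and follow-up assessments at weeks 5 and 12". Table 1 schedules both instruments at baseline, week 5 and week 12. Under Recruitment, "the participants will complete the baseline online assessment and then will be randomly allocated to either the intervention or the control group", so the baseline scores precede randomisation.

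**The concern.** Because baseline is measured before allocation, the expected difference between arms at pretest is zero. A model that treats pretest as one of three outcomes spends part of its information on an occasion where there is no effect to find.

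Two things follow. The interaction is a 2-df omnibus test. Its visit-level components are differences in raw change scores, which are noisier than baseline-adjusted differences whenever r is below 1. The group main effect averages over all three occasions, pretest included, so it is not the effect at either follow-up. At stake are the power of the primary comparison and how directly the reported result answers the stated outcome, for each of PHQ-9 and GAD-7.

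**Working it through.** **Inputs from the article (Sample Size).** Power 80%, 95% confidence with a two-sided formula, SD 9.865, means 21.1 and 16.2, 64 per group, 30% dropout, 84 per group.

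**The plan's own figure.** n = 2 × 9.865² × (1.960 + 0.842)² / 4.9² = 63.6, so 64 per group. Then 64 × 1.3 = 83.2, so 84. Both reproduce. The formula compares two means at one time; it corresponds to no single term of the mixed ANOVA.

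**Assumptions for the comparison.**
- N = 58 evaluable per arm (84 × 0.70 = 58.8, rounded down).
- Effect d = 0.5 SD (4.9 / 9.865 = 0.497), equal at weeks 5 and 12.
- Equal variances and a common correlation r between all occasions (compound symmetry). The article gives no r, so 0.3 to 0.7 is shown.
- b = N d² / 2 = 58 × 0.25 / 2 = 7.25.

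**Step 1. Variance of the treatment contrast at one visit** (in units of the score variance).
- Change score: 2(1 − r).
- Baseline-adjusted: 1 − r².
- Ratio: (1 − r²) / [2(1 − r)] = (1 + r)/2.

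| r | change score | adjusted | ratio |
|---|---|---|---|
| 0.3 | 1.40 | 0.91 | 65% |
| 0.5 | 1.00 | 0.75 | 75% |
| 0.6 | 0.80 | 0.64 | 80% |
| 0.7 | 0.60 | 0.51 | 85% |

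**Step 2. Noncentrality of each test, sustained effect** (value at r = 0.5).
- Interaction, 2 df: b(2/3)/(1 − r) = 9.67.
- ANCOVA at one visit, 1 df: b/(1 − r²) = 9.67.
- Baseline-adjusted test of both visits, 2 df: 2b/[(1 − r)(1 + 2r)] = 14.50.
- Baseline-adjusted ANCOVA on the mean of both visits, 1 df: also 14.50.

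**Step 3. Power from the noncentral F, 5% level.**

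| Test | r = 0.3 | r = 0.5 | r = 0.7 |
|---|---|---|---|
| Group-by-time, 2 df | 64% | 80% | 96% |
| ANCOVA at one visit, 1 df | 80% | 87% | 96% |
| Adjusted, both visits, 2 df | 90% | 93% | 98% |
| ANCOVA on mean of both visits, 1 df | 95% | 97% | 99% |

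The first and third rows are the like-for-like pair: both use 2 df and both use both visits. Their noncentralities differ by the factor 3/(1 + 2r), which is 1.88, 1.50 and 1.25 at r = 0.3, 0.5 and 0.7.

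**Step 4. Effect halved at one of the two visits.** The interaction has 51%, 67% and 88% at r = 0.3, 0.5 and 0.7; the 2-df adjusted test has 74%, 81% and 93%. By symmetry it does not matter which visit carries the smaller effect. It matters a great deal for a single-visit ANCOVA: at r = 0.5 it has 87% at the full-effect visit and 34% at the other.

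**Step 5. Group main effect, only if it were used for efficacy.** It estimates (0 + d + d)/3 = 2d/3, so 4.9 points become 3.27. Noncentrality is b(4/9)/[(1 + 2r)/3], and power is 68%, 59% and 51% at r = 0.3, 0.5 and 0.7.

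**The case against.** The strongest reply is that the plan is conventional and valid. The interaction is the term that matches an outcome defined as change. Its contrasts, week 5 minus pretest and week 12 minus pretest, are exactly the between-arm differences in the stated change scores, and they already remove chance baseline imbalance. So baseline is used, though not in the most efficient way. All of this stands. Visit-level contrasts and confidence intervals are also details that a condensed article may leave to a fuller document, so their absence is not counted here.

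The size of the gain rests on an assumed correlation, and that stands too. With a sustained effect the interaction matches a one-visit ANCOVA at r = 0.7 (96% each), and the baseline-adjusted test of both visits then adds only about two points.

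A reader might go further and infer that the plan dilutes the treatment effect to two thirds, or lets baseline imbalance distort the efficacy result. The article does not support that: it never says efficacy will rest on the group main effect, and the interaction has neither problem. A reader might also set 67% for the interaction against 87% for ANCOVA at week 5 when the effect halves by week 12. That comparison picks the favourable visit. The article names both weeks, and ANCOVA at the weaker visit has only 34%.

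What the reply does not remove is the like-for-like gap, which favours baseline adjustment at every correlation shown, whether the effect is sustained or halved at one visit.

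**Conclusion.** The point holds as one of efficiency and clarity. The planned interaction test is valid, but it is less precise than an analysis using the same data with baseline as covariate. At 58 per arm and 0.5 SD sustained, the like-for-like difference is 26 points of power at r = 0.3 (64% against 90%), 13 at r = 0.5 (80% against 93%) and 2 at r = 0.7 (96% against 98%). These figures depend on the assumed correlation, compound symmetry, effect size and number evaluable. The direction does not depend on the value of r: the ratio (1 + r)/2 is below 1 for any r below 1. Separately, the text does not say which model term is decisive, and one candidate, the group main effect, would not estimate the stated outcome. This is an improvement worth making, not a flaw that invalidates the plan.

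**What to change.** For each of PHQ-9 and GAD-7, model the week 5 and week 12 scores as outcomes, with arm, visit, arm-by-visit, baseline score and baseline-by-visit as terms. The outcome definition need not change: once baseline is a covariate, the arm difference in the follow-up score and in the change score are the same quantity.

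Name one primary contrast per outcome, either one visit or the average of weeks 5 and 12, and report the adjusted difference with its 95% CI at each visit. Do not use the group main effect from a model that includes pretest as evidence of efficacy.

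The article reports data collection complete and analysis not yet completed, so the choice should be dated and recorded as made before comparative results are seen. The cost is analysis wording only; the baseline scores are already scheduled for every participant.

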### Trial

The trial will be conducted using the Internet as a medium of implementation of the psychoeducation intervention program. The planning of the study started on March 1, 2013, and data collection is expected to be complete on August 14, 2014. At the point of submitting this paper for publication, data analysis had not yet been completed.

### Ethics Approval and Registration

This study was approved by the University Research Ethics Committee of Universiti Putra Malaysia on August 14, 2013 (Reference No: UPM/TNCPI/RMC/1.4.18.1 JKEUPM). The study is registered in the Malaysian National Medical Research Registry (NMRR-14-698-21864) and in the ISRCTN registry (ISRCTN39656144). Consent will be obtained from all the participants who are willing to participate in the study.

## Results

By the time the manuscript was submitted to the journal, data collection was completed. The results are expected to be published in late 2015 or early 2016.

## Discussion

This RCT study protocol is aimed to investigate the effectiveness of a Web-based psychoeducational intervention for depressive and anxiety symptoms for the adult community in Selangor, Malaysia. Self-management through the Internet offers the opportunity to reach and treat the community who may suffer from mild-to-moderate depression and anxiety, and for those who are reluctant to seek for assistance from medical professionals. In addition, it can serve as an appealing modality for quick help to manage these problems. Web-based programs can provide the advantage of disclosing certain information better than face-to-face interviews. Moreover, information can be accessed 24/7 and is available to a wider community. This can be very useful when an immediate need is required for information on management.

To our knowledge, Internet-based management for both depression and anxiety in the community has not been studied in Malaysia. This study could give an insight on the effectiveness and applicability of a Web-based psychoeducation program in the current population. The strength of this study is that the psychoeducational intervention program is developed based on the predictors of depression [22] and anxiety in our own population. The program aims to address the predictors that contribute to depression and anxiety in our community. This brief Web-based program will enable the community to use easy, user-friendly, valid, and reliable tools for assessing their mental health status.

Second, the availability of the program in both English and Malay languages is an additional plus point. Participants can choose their preference language to complete the sessions. Third, the assessments are available in both languages and have been validated in our population. Fourth, the intervention program was designed to be as brief as possible to increase the acceptability of the program versus other lengthier interventions, which could further increase the dropout rates.

Nevertheless, there are some limitations in this study. One potential limitation of this study is the nature of a Web-based program itself. The Web-based program will be restricted only to those who are literate and who have access to the Internet. Although its use will be limited to people who are computer literate and who have access to the Internet, this population is increasing significantly in Malaysia. Therefore, a great number of people will be able to access this Web-based assessment and intervention program, and use it for assessment of their own mental health and seek help when required. A second limitation is assurance cannot be made that the selected participants will complete the study by themselves. However, by having a specific username and password to log in to the system, this problem would be minimized. Another potential limitation is the short duration of follow-up to assess the effect of the intervention program. However, studies have shown that effectiveness can be shown even with shorter durations [19].

The Web-based psychoeducation program could serve as a new modality to manage mild-to-moderate depression and anxiety. Our study aims to provide better recognition and management of depressive and anxiety symptoms. It also aims to educate and create awareness about depression and anxiety in the community. Depression and anxiety are the most common mental health disorders. There is a need to develop simple, brief, and effective interventions tailored to the needs of the community to reduce the burden of these disorders.

## Abbreviations

CBT: cognitive behavioral therapy
DSM-IV: Diagnostic and Statistical Manual of Mental Disorders (Fourth Edition)
GAD: generalized anxiety disorder
GAD-7: Generalized Anxiety Disorder 7
MHLQ: Mental Health Literacy Questionnaire
PHQ-9: Patient Health Questionnaire 9
RCT: randomized controlled trial
